## Transcriptome analysis

6

### RNA extraction, library preparation and sequencing

6.1

The extraction of RNA commenced with the utilization of TRIzol reagent (Invitrogen, Carlsbad, CA, USA), conducted in strict adherence to the manufacturer's stipulated procedures. Subsequent to extraction, the Nanodrop instrument facilitated an evaluation of the quality and concentration of the obtained RNA. Additionally, the Agilent 2100 Bioanalyzer (Agilent, CA, USA) was employed to assess RNA integrity, with only samples exhibiting a RNA integrity number (RIN) surpassing 7 deemed suitable for subsequent RNA library constitution and ensuing analyses.

Library construction transpired through the application of the Illumina TruSeq Stranded mRNA Library Prep Kit (Illumina, CA, USA), aligning with the manufacturer's directives. This process initiated by enriching mRNA molecules with polyA tails through the use of magnetic beads, effectively eliminating ribosomal RNA (rRNA) and other non-coding RNA species. Subsequent steps included reverse transcription employing random hexamer primers for synthesizing the first strand of cDNA, succeeded by DNA polymerase-mediated synthesis of the second cDNA, ultimately generating double-stranded cDNA molecules. The ensuing steps involved end repair and A-tailing, followed by the ligation of Illumina TruSeq index adapters. To enhance the library, PCR amplification was executed, thereby augmenting the quantity of cDNA fragments available for sequencing. The thorough assessment of library quality and size distribution was conducted using the Agilent 2100 Bioanalyzer.

Sequencing procedures were carried out on the Illumina NovoSeq 6000 platform, employing paired-end 150 bp reads. The resultant sequencing data, formatted in FASTQ, underwent quality control via the FastQC software.

### Bioinformatic and statistical analysis

6.2

Quantification of RNA sequencing data was executed utilizing the kallisto software [22]. Differential expression analysis was conducted with the DESeq2 package [23] to identify genes with distinct expression patterns. Additionally, the cluster Profiler package [24]

was employed to enhance the analysis of differentially expressed genes.

Continuous variables' normality was assessed using the Shapiro-Wilk test in this study. For normally distributed continuous variables, data were presented as mean ± SD (standard deviation), and intergroup comparisons utilized Student's t-test. Conversely, skewed continuous variables were expressed as median (interquartile range, IQR) and compared through the nonparametric Wilcoxon rank-sum test. Categorical variables were reported as frequencies (percentages, %) and subjected to comparison via the chi-square test.

To explore associations between gene abundance and various clinical indicators pertaining to ovarian reserve, ovarian endocrine function, and perimenopausal syndrome symptoms, Pearson's correlation analysis was employed. For genes exhibiting significant differences, receiver operating characteristic (ROC) curves were constructed to assess their diagnostic performance. The area under the curve (AUC) value served as a metric for discriminatory power. Statistical significance was set at a two-tailed *P* < 0.05. R software was utilized for all data analyses.

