### Secondary outcomes

5.2

The principal outcome measure in this study revolves around the alteration observed in FSH levels. This metric serves as a pivotal gauge to evaluate the effectiveness of acupuncture treatment when employed as an adjunctive therapy for POI. The data collection process is bifurcated into two distinct time points: the baseline assessment conducted prior to the study's initiation and a subsequent assessment following the culmination of three menstrual cycles of acupuncture treatments. This meticulous approach aims to provide comprehensive insights into the impact of acupuncture on FSH levels over the specified duration, thereby contributing to the overall assessment of its therapeutic efficacy for POI. In conjunction with the primary focus on FSH levels, this study encompasses an exploration of secondary outcomes to foster a holistic comprehension of acupuncture's impact on POI. Secondary outcome measures encompass biometric features, hormone biomarkers, Self-Rating Anxiety Scale, Self-Rating Depression Scale, and transcriptome analysis. The data acquisition for these secondary outcomes is structured around two pivotal time points: the baseline assessment before study commencement and the post-intervention assessment after the conclusion of acupuncture sessions.

Comparative analysis of these datasets enables researchers to discern alterations in various parameters resultant from acupuncture treatment. Specifically, to scrutinize the distinct genes associated with individual variations in acupuncture's therapeutic effects, gene abundance profiling will be conducted within the study group and juxtaposed with the control group. Transcriptome analysis, performed on peripheral blood samples from 5 participants in each group exhibiting a ≥30 % reduction or <30 % reduction in serum FSH levels post-intervention, aims to unravel the molecular intricacies underlying acupuncture's differential efficacy. An additional 10 subjects, meeting the study criteria, will be enlisted for the healthy control group. The ensuing data analysis will be executed utilizing SPSS 25.0 for comprehensive evaluation.

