### Sample size

6.4

The calculation of the sample size is derived from the formula comparing two sample rates：$$N=\frac{{\left(Z_{1-\alpha \;}+Z_{1-\beta }\right)}^{2}\left(1+\frac{1}{k}\right)\cdot \sigma^{2}}{{\left(\mu_{T\;}-\mu_{C}-△\right)}^{2}})$$

Here, N represents the required sample size for each group, Pe and *Pc* denote the maximum and minimum effective rates of each group. Based on our retrospective clinical data and previous experimental reports, acupuncture demonstrated a reduction in FSH levels by 20 IU/L, while assuming that the control group reduced FSH levels by 14.5 IU/L. For the study, which is divided into two groups with parameters $\mu_{T\;}$ = 20, $\mu_{C}$ = 14.5, △=3, a test level α = 0.05 and a test efficiency 1-β = 0.9 were considered.

In light of an anticipated 20 % dropout rate, a total of 108 patients will be recruited, ensuring no less than 54 participants in each group. Given the absence of a standardized sample size calculation for transcriptome analysis, the approach aligns with prevalent studies on POI. From the pool of 108 participants, 10 patients in each group (comprising 5 with a decrease of ≥30 % in serum FSH levels after intervention, 5 with a decrease of <30 % in serum FSH levels after intervention, and 10 normal female volunteers in the healthy control group) will be selected for transcriptome analysis.

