### Statistical methods

6.7

Data analysis will be executed utilizing SPSS version 25.0 (SPSS Inc., Chicago, IL, USA) by two qualified statisticians, ensuring the attainment of robust and reliable results.Descriptive statistics, comprising mean, median, 25th percentile, 75th percentile, standard deviation, maximum values, and minimum values, will be employed to present the results of the measurement data analysis. Group comparisons will be facilitated using either the independent sample *t*-test or the Mann-Whitney U rank sum test, contingent upon the normal distribution and homogeneous variance of the measurement data. Enumeration data will be characterized by frequency and constituent ratios, with group comparisons executed through Pearson's χ2 test or Fisher's exact test. Correlations between different indicators will be explored through Pearson and Spearman correlations. A significance threshold of P < 0.05, employing a two-sided test, will dictate statistical significance. Additionally, metagenomic analysis of the gut microbiome will be conducted by BGI Shenzhen Co., Ltd (China).

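### Section 6.2 gives P < 0.05 as its only significance rule for a genome-wide screen, mentions no false-discovery control, and scores the selected genes by AUC in the samples that selected them

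*Protocol article*

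**What the plan says.** Section 6.2 (Bioinformatic and statistical analysis) sets out the transcriptome analysis in some detail. On differential expression it says: "Differential expression analysis was conducted with the DESeq2 package [23] to identify genes with distinct expression patterns". It then plans Pearson correlations between gene abundance and clinical indicators, and an ROC step: "For genes exhibiting significant differences, receiver operating characteristic (ROC) curves were constructed to assess their diagnostic performance". The measure is fixed as well: "The area under the curve (AUC) value served as a metric for discriminatory power". The same paragraph closes with its only decision rule: "Statistical significance was set at a two-tailed *P* < 0.05". Section 6.7 (Statistical methods) repeats the rule for the trial as a whole: "A significance threshold of P < 0.05, employing a two-sided test, will dictate statistical significance".

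Section 6.4 (Sample size) gives the composition of each treatment group's sequenced subset: "comprising 5 with a decrease of ≥30 % in serum FSH levels after intervention, 5 with a decrease of <30 % in serum FSH levels after intervention". Ten healthy women are added. Section 5.2 (Secondary outcomes) and the note to Fig. 1 describe the same samples.

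The article mentions no adjusted P value, false-discovery rate, cross-validation, hold-out set or second cohort. It does not say which comparison the ROC curves use.

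**The concern.** There are two separate problems.

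**Multiplicity.** A transcriptome screen tests thousands of genes, and the correlations multiply that by the number of clinical indicators. A 5 % threshold applied gene by gene lets through about 5 % of all genes that have no effect. P < 0.05 is the only rule printed.

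**Circularity.** A gene is selected because its expression differs between two groups of women, and its AUC is then computed for separating groups of those same women. A gene that has passed the first step must score well on the second if the contrast is the same. The AUC restates the selection and does not test it independently.

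Finding genes linked to individual response to acupuncture is a headline aim in the abstract and the Background. If both problems stand, chance genes could be reported with AUCs that appear to confirm them.

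**Working it through.** The article gives no error rate, gene count or AUC target for the transcriptome analysis, so there is no figure of its own to reproduce. The calculated main-trial sample size (108) does not bear on this point.

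**Inputs**
- Threshold 0.05, two-sided (sections 6.2 and 6.7).
- Group sizes: 5 versus 5 by FSH response within an arm; 10 versus 10 by arm, or one arm against healthy women; 20 versus 10 for all POI against healthy (sections 5.2 and 6.4, Fig. 1 note).
- Number of tested genes: not in the article. Assumed 10,000 to 20,000.
- No true signal; independent, normally distributed genes; a t-test standing in for DESeq2. These are also assumptions.

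**Step 1. Exact chance AUC, 5 versus 5, either direction.** AUC = U/(5 × 5), where U is the Mann-Whitney statistic. There are C(10,5) = 252 equally likely rank arrangements under no effect.
- AUC = 1: 2/252 = 0.79 %, so 79 to 159 genes.
- AUC ≥ 0.96: 4/252 = 1.59 %, so 159 to 317 genes.
- AUC ≥ 0.92: 8/252 = 3.17 %, so 317 to 635 genes.

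**Step 2. The same at 10 versus 10.** C(20,10) = 184,756.
- AUC = 1: 2/184,756 = 0.001 %, so 0.1 to 0.2 genes.
- AUC ≥ 0.95: 0.02 %, so 2 to 4 genes.
- AUC ≥ 0.90: 0.15 %, so 15 to 30 genes.

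**Step 3. Select, then score in the same samples.** Simulation of 200,000 null genes with raw P < 0.05; counts scaled to 10,000 and 20,000 genes:

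| Contrast | Pass P < 0.05 | Mean apparent AUC of those passing | Pass and AUC ≥ 0.96 | Pass and AUC = 1 |
|---|---|---|---|---|
| 5 v 5 | 493 to 986 | 0.92 | 156 to 313 | 80 to 160 |
| 10 v 10 | 503 to 1,006 | 0.79 | 1.2 to 2.3 | 0 |

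At 5 versus 5, 99.9 % of the selected null genes have an apparent AUC of at least 0.80. At 20 versus 10 the mean is about 0.75 and none reach 1.

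**Step 4. Effect of false-discovery control.** With 15,000 null genes at 5 versus 5, raw P < 0.05 passes about 740. Benjamini-Hochberg at 5 % leaves an average of 0.05 per analysis (0.1 at 10 versus 10). This removes the chance genes. It does not remove the optimism in the AUC of a gene that does pass, because passing still requires a large observed difference in the same women.

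**Step 5. Precision without selection.** For an AUC of 0.90 with 5 and 5, the Hanley-McNeil variance is [A(1−A) + 4(Q₁−A²) + 4(Q₂−A²)]/25, with Q₁ = A/(2−A) = 0.818 and Q₂ = 2A²/(1+A) = 0.853. The standard error is about 0.11, which is too imprecise to support a diagnostic claim.

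**The case against.** The strongest reply is that the text does not say what a critical reader might infer.

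- **Raw P values.** A reader might conclude that genes are called on unadjusted P. Section 6.2 does not say so. DESeq2 can supply Benjamini-Hochberg adjusted P values, it is named in a separate paragraph without a threshold, and the P < 0.05 sentence comes later, after the conventional tests. The wording fits either reading, and with adjusted P the flood of chance genes disappears. This stands. It does not rescue the separate gene-by-clinical correlations, which DESeq2 does not adjust.
- **ROC on 5 versus 5.** A reader might assume this because the subsets are built from responders and non-responders and individual response is the stated question. No contrast is attached to the ROC step, and a diagnostic comparison could equally mean POI against healthy women. This stands, so it cannot be said that hundreds of genes will show an AUC near 1.
- **Left to a fuller document.** An article may leave detail to the full protocol or analysis plan. Here, though, the article does state a threshold and an ROC procedure. The point concerns what those two statements produce together.
- **Importance.** The transcriptome is a secondary outcome, and the Discussion concedes its modest sample size. That lowers the weight of the point. The Discussion does not mention multiplicity or selection bias.

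**Conclusion.** The point holds in this form. Section 6.2 prints one threshold, unsuited on its own to a genome-wide screen and to the accompanying correlations, mentions no false-discovery control, and measures AUC in the only samples described. Upward bias in the AUC follows whichever P value was intended.

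The number of chance genes is conditional. With raw P, a 5-versus-5 contrast, 10,000 to 20,000 tested genes and no true signal, expect about 500 to 1,000 false genes with a mean apparent AUC of 0.92. About 160 to 320 of them would be at 0.96 or above, and 80 to 160 exactly at 1. With raw P at 10 versus 10, a similar number pass, with a mean of about 0.79 and almost none near 1. With adjusted P, chance genes fall to about zero. These are expectations; expression is correlated between genes, so realised counts would vary widely around them.

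This should be fixed, but the primary FSH comparison does not depend on it.

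**What to change.** Amend section 6.2 as follows:

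1. Name each transcriptome contrast. Define a significant gene by Benjamini-Hochberg adjusted P (FDR 5 %) within that contrast.
2. Apply the same control to the gene-by-clinical-indicator correlations.
3. State which contrast the ROC curves use.
4. Remove the diagnostic-performance claim. Either omit the ROC, or report it as a descriptive, hypothesis-generating apparent AUC that needs validation in independent samples.

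Leave-one-out AUC with gene selection repeated in each fold is the usual suggestion, but it does not work at 5 versus 5. In null simulations its mean ranged from about 0.27 to 0.45, depending on the set-up, where 0.50 would be correct. Its standard deviation was about 0.25 to 0.3. It replaces an upward bias with a downward one and is too noisy to interpret.

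The cost is a few lines of text and minor programming. The drawback is that fewer genes will be declared.

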### Adverse events

6.3

The emphasis on safety in this clinical trial is paramount, particularly concerning acupuncture interventions. Adverse events related to acupuncture primarily involve local ecchymoses, fainting, significant pain, and local infections. These events are closely tied to patients' subjective experiences and the proficiency of acupuncturists in their needling techniques. To ensure a secure operation throughout the trial, all participating acupuncturists will undergo comprehensive pretrial training and must successfully pass training and assessment to ensure uniform standards.

Throughout the treatment process, any adverse events stemming from acupuncture will be meticulously recorded. Operators will respond promptly and appropriately, implementing necessary measures to address adverse events as they arise. In cases where serious adverse events occur, investigators will take immediate action to suspend the clinical trial. Swift administration of effective treatments will follow to manage and mitigate the severity of the event. Furthermore, any occurrence of serious adverse events will be promptly reported to the ethical review board at the Shenzhen Maternity and Child Healthcare Hospital within 24 h. The entire process, encompassing details of adverse events and their management, will be meticulously documented for comprehensive record-keeping and subsequent analysis.

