**Methods/design:**

Constituting an open-label, nested case-control study, this research endeavors to enroll 108 women diagnosed with POI. Participants will be randomly assigned in a 1:1 ratio to either the study group or the control group, each comprising 54 subjects. Ten patients from each group meeting specific criteria will partake in transcriptome analysis. An additional 10 subjects meeting the study criteria will form a healthy control group. The study group will exclusively undergo acupuncture treatment, while the control group will solely receive Fenmutong. Acupuncture sessions, administered thrice weekly across three menstrual cycles from the fifth day of menstruation, constitute the intervention. Primary outcome measurement rests on Follicle-Stimulating Hormone (FSH) levels, supplemented by secondary assessments encompassing biometric features, hormone biomarkers, anxiety and depression scores, and transcriptome analysis. Baseline measurements precede intervention, with post-intervention evaluations following. The study endeavors to discern specific genes linked to individualized responses to acupuncture. Data analysis, employing SPSS 25.0 software, incorporates a meticulous examination of peripheral blood samples for transcriptome analysis. The investigation aspires to shed light on genetic determinants influencing the effects of acupuncture on women with POI, thereby fostering elevated standards in patient care and management.

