## Strengths and limitations of this study

1

This protocol aims to provide patients, clinical practitioners and policy makers with more evidence on the efficacy and safety of acupuncture in the treatment of 108 POIs.

The data extraction and management, assessment of risk of bias sections will be carried out by two or more researchers independently.

The non-inclusion of studies published in languages other than English and Chinese may result in limitations related to publication bias.

Multiple types of acupuncture therapies may increase the risk of heterogeneity.

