## Background

3

Premature ovarian insufficiency (POI) has experienced a notable surge in prevalence [1,2], affecting around 6 million Chinese women under 40 years, and emerges as a significant contributor to reproductive disorders and female infertility [3].

Conventional treatments such as hormone replacement therapy (HRT) and Fenmutong, while commonly employed, may yield unsatisfactory outcomes and are associated with notable side effects [4,5]. Consequently, a growing number of POI patients seek complementary and alternative medical (CAM) methods, including acupuncture, reflecting a quest for safer and potentially more effective interventions [6,7].

Acupuncture, a longstanding component of complementary and alternative medicine, has demonstrated promising effects in treating POI [8]. It activates the neural-endocrine-immune network, leading to increased beta-endorphin production, thus influencing the endocrine system and hormones. The appeal of acupuncture lies in its minimal side effects, safety, and cost-effectiveness, potentially addressing the root cause of the condition. Our research team has dedicated considerable effort to studying POI, with previous observations indicating that acupuncture not only alleviate perimenopausal symptoms, restore the menstrual cycle, and regulate serum hormone levels [[9], [10], [11], [12]]. Young patients with relatively good ovarian reserve function appear to experience more favorable treatment outcomes [13]. Conversely, older patients or those with relatively poor ovarian reserve function have also demonstrated improved efficacy with acupuncture therapy for POI, suggesting individual variability as a potential key factor influencing treatment outcomes [14,15]. Despite these observations, the underlying cause of individual response differences to acupuncture in women with POI remains unexplored.

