### Study design

4.1

The proposed investigation adopts an open-label, nested case-control study design to be conducted at Shenzhen Maternity and Child Healthcare Hospital. A total of 108 participants diagnosed with POI will be recruited for the study, and subsequent random assignment will be executed to allocate these patients into either the study group or the control group. The allocation ratio is set at 1:1, ensuring an equal distribution of 54 subjects in each group. Prior to the commencement of any intervention, explicit informed consent will be procured from all participating patients through the endorsement of a consent form administered by the researchers.

Patients comprising the study group will exclusively undergo acupuncture treatment, while those in the control group will exclusively receive Fenmutong. To gain deeper insights into the mechanisms contributing to individual variations in the therapeutic outcomes of acupuncture, a subset of 10 patients from each group will undergo transcriptome analysis. This subset will encompass patients experiencing a serum FSH level decrease of ≥30 % post-acupuncture intervention, alongside those displaying a decrease of <30 % in serum FSH levels following the intervention. The trial's procedural flow is visually represented in Fig. 1, offering a comprehensive overview of the various stages and interventions integral to the study. Additionally, Table 1 provides meticulous details on the data collection process, delineating specific data points and measurements crucial for the comprehensive execution of the research.

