**Fig. 1 fig1:**
[figure not shown]
Study flow chart. Note: transcriptome analysis included 10 patients in the POI group and 10 patients in the Fenmutong group, with 5 patients with serum FSH levels ≥30 % and 5 patients with serum FSH levels <30 % in both groups.10 healthy women were selected as the control group.

**Table 1 tbl1:** Overview of study visits.

Itern	Screening visit	Baseline visit	Treatment visit		End of treatment visit
			POI group	Control group	
Sign consent	×				
History	×				×
Biometric features	×	×			×
Transvaginal ultrasound	×	×	×	×	×
Routine test	×				×
hormone biomarkers		×			×
transcriptome analysis		×			×
Questionnaires		×			×
Acupuncture treatment			×		
Adverse events			×		

Note: Participants from the POI group will be selected for transcriptome analysis and will only be assessed at the initial screening visit. History, biometric features, routine test results, and transcriptome analysis will be assessed. Biometric features include body mass index (BMI); transvaginal ultrasound includes endometrial thickness, ovarian volume, antral follicle count, and size of ovarian cysts or developing follicles; Routine tests include blood routine examination, liver function, kidney function, routine stool, and urine tests; Hormone biomarkers include luteinizing hormone (FSH), follicle stimulating hormone (LH), total testosterone, progesterone, estradiol, and leptin; questionnaires include Self-Rating Anxiety Scale (SAS) and Self-Rating Depression Scale (SDS).

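### Non-serious adverse events are recorded only in the acupuncture arm and only when attributed to acupuncture, so their rates cannot be compared between arms without bias

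*Protocol article*

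**What the plan says.** Section 6.3 (Adverse events) gives one rule for recording ordinary events: "any adverse events stemming from acupuncture will be meticulously recorded". The expected events it names all come from needling: "Adverse events related to acupuncture primarily involve local ecchymoses, fainting, significant pain, and local infections". It has no corresponding sentence for Fenmutong. The same section sends every serious adverse event to the ethics board within 24 hours and does not limit this by arm or cause.

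The visit schedule in Table 1 has a row labelled "Adverse events" with a single mark, at the treatment visit in the POI group column.

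The comparator is an active drug: the Abstract states that "the control group will solely receive Fenmutong", and section 4.7 describes estradiol followed by estradiol with dydrogesterone over three cycles. The Background says that conventional treatments, Fenmutong among them, "are associated with notable side effects", and it recommends acupuncture partly for its tolerability. Section 1 says the work should give "more evidence on the efficacy and safety of acupuncture".

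**The concern.** Collection is asymmetric in two ways. First, ordinary events have a scheduled place in one arm only. Second, within that arm an event qualifies only if it is thought to come from acupuncture, so causality is decided before the event is written down.

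The article's case for acupuncture rests partly on side effects, yet ordinary events are sought only in the arm presumed safer. A safety table built on this rule could mislead in either direction. It could show events for acupuncture alone, which makes acupuncture look worse. Or it could show a low acupuncture count, filtered by attribution, that is then set against the general reputation of hormone treatment. No later analysis can repair this, because events never recorded cannot be recovered.

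**Working it through.** The article gives no figure to reproduce here. The check compares the text with the table and then looks at what the rule does to an estimate.

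**1. Which arm the mark belongs to.** The note to Fig. 1 refers to "10 patients in the POI group and 10 patients in the Fenmutong group", so in that figure the POI group is the acupuncture arm. In Table 1 the acupuncture-treatment row is also marked only under the POI group, which fits.

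**2. The Table 1 rows side by side.**

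| Row | Screening | Baseline | Treatment, POI group | Treatment, control | End of treatment |
|---|---|---|---|---|---|
| Adverse events | – | – | × | – | – |
| Acupuncture treatment | – | – | × | – | – |
| Transvaginal ultrasound | × | × | × | × | × |
| Routine test | × | – | – | – | × |

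The ultrasound row shows that the control column is filled where a procedure applies, and that control women have a treatment visit. The adverse-event row has the same pattern as the acupuncture-treatment row. Text and table therefore say the same thing.

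**3. How many women are affected.** Section 4.1: "The allocation ratio is set at 1:1, ensuring an equal distribution of 54 subjects in each group". Share with no scheduled recording of non-serious events: 54/108 = 0.50.

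**4. What control women do have.**
- Serious-event reporting within 24 hours (section 6.3), not limited by arm.
- Routine blood, liver, kidney, stool and urine tests at screening and end of treatment (Table 1), not split by arm.
- Reporting of withdrawals with reasons (section 6.6).

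These would catch a serious event, a laboratory abnormality at the final visit, or a complaint bad enough to make a woman leave. None is a systematic enquiry about non-serious symptoms during treatment.

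**5. Effect on a between-arm comparison.** Let pA and pF be the true risks of a non-serious event under acupuncture and Fenmutong, and rA and rF the probabilities that such an event is recorded. The recorded difference is rA·pA − rF·pF. If the true risks are equal (pA = pF = p), it becomes (rA − rF)·p, which is zero only if rA = rF. The plan makes the two differ by design: rF has no scheduled collection behind it, and rA is lowered by the attribution condition. Neither can be estimated from the data collected, so the bias cannot be corrected and its direction is not known in advance.

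**The case against.** The strongest reply is that the Fenmutong arm is not unmonitored. That stands. A reader might infer from the blank cell that half the trial has no safety record, but the serious-event rule, the end-of-treatment laboratory tests and the withdrawal reasons all cover both arms. A reader might also infer that serious events in control women have no reporting route. Section 6.3 says otherwise, since its 24-hour rule applies to any serious event.

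It is equally tempting to say that unblinded operators decide which events count. The article does not say who judges attribution. It says operators respond to events, section 6.6 gives CRF recording to trained data collectors, and section 6.5 says staff other than patients and acupuncturists are to be kept blinded. What is stated is the attribution condition itself, and that is enough for the point.

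A further reply is that Table 1 is imperfect: it has no row for Fenmutong administration, and its note swaps the names of FSH and LH. Section 6.3 also stresses acupuncture without expressly excluding the other arm, and the full protocol may contain more. This lowers the weight of the blank cell taken alone. However, the wording of section 6.3 points the same way independently, so the article states a one-sided rule and does not merely omit detail.

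Finally, no safety outcome is defined in section 5 and no between-arm safety test is planned. Section 1 speaks of the safety of acupuncture, not relative safety, and several of its other items read like text for a systematic review. That limits the consequence: no planned analysis fails. It does not remove the problem for the account of tolerability that the Background invites.

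**Conclusion.** The point holds for non-serious adverse events. Their systematic recording is planned in one arm of two, leaving 54 of 108 randomised women (50 %) without it, and in the other arm it is restricted to events attributed to acupuncture. Non-serious event rates therefore cannot be compared between arms without bias, and the acupuncture arm's own count may be too low. Serious-event reporting and the FSH primary outcome are not affected.

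The conclusion assumes that the POI group column in Table 1 is the acupuncture arm, as the Fig. 1 note and the acupuncture-treatment row indicate, and that the article reports the collection rule of the full protocol faithfully. If the full protocol already records all events in both arms, only the article needs correcting.

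**What to change.** - **Section 6.3:** record all adverse events regardless of presumed cause, with the same prompts at the treatment and end-of-treatment visits in both arms. Assess relatedness as a separate, later item on the form.
- **Table 1:** mark the control-group and end-of-treatment cells of the adverse-event row.
- **Reporting:** tabulate events by arm. Base the comparison on the prompted visits common to both arms, because acupuncture women attend three times a week and have more occasions to volunteer a complaint.

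The serious-event rule already covers both arms and needs no change. The cost is one extra CRF page for control women at visits already planned. No treatment, visit or sample size changes. The article says the trial began in March 2023, so for women who finish before the change the gap cannot be filled afterwards. It should be stated as a limitation, with the number affected in each arm.
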